## Abstract

**Background:**

Chronic low back pain (CLBP) is a global health problem associated with an increasing burden on individuals, health care systems, and society. Common treatments for people with CLBP produce, on average, small short-term improvements in pain and function compared with minimal care. The RESOLVE trial randomly allocated 276 people with CLBP to a new complex treatment strategy, pain education integrated with graded sensorimotor precision training (RESOLVE), or a sham control. The RESOLVE treatment was developed within a theoretical framework to target possible treatment mechanisms associated with CLBP development and persistence.

**Objective:**

This protocol describes the planned evaluation of these proposed treatment mechanisms. Improved understanding of the mechanisms underpinning the RESOLVE treatment may guide its refinement and implementation.

**Methods:**

We will use causal mediation analysis to evaluate the proposed treatment mechanisms, including pain self-efficacy, back beliefs, pain catastrophizing, kinesiophobia, back perception, tactile acuity, and movement coordination. The primary outcomes are pain intensity and function at 18 weeks following allocation. Data were collected blind to allocation and hypotheses at baseline (mediators, outcomes, confounders), end of treatment (mediators), and at 18 weeks following allocation (outcomes). We will test the robustness of our findings by conducting planned sensitivity analyses.

**Results:**

Ethical approval was granted by the University of New South Wales Human Research Ethics Committee (HC15357). A total of 276 participants have been recruited from primary care practices and the community in Sydney, Australia.

**Conclusions:**

The RESOLVE treatment constitutes a new paradigm for CLBP management with potentially wide-reaching implications. This mechanistic evaluation will provide evidence for the hypothesized treatment mechanisms and help explain why the treatment strategy did or did not have an effect on patient-reported outcomes. These results will help guide the treatment refinement and implementation.

**Trial Registration:**

Australian and New Zealand Clinical Trials Registry ACTRN12615000610538; https://www.anzctr.org.au/Trial/Registration/TrialReview.aspx?id=368619&isReview=true

**International Registered Report Identifier (IRRID):**

DERR1-10.2196/26053

## Introduction

Low back pain (LBP) is a global health problem [1,2]. The associated personal and societal burden continues to increase, despite the increasing amount of health care resources devoted to LBP treatment [3,4]. Although many recover from a new episode of LBP, recurrence is common, and for a small proportion pain becomes persistent and significantly disabling [5-7]. Individuals who develop chronic low back pain (CLBP) have a reduced chance of recovery and experience substantial functional limitations and poor quality of life [8,9].

People with LBP perceive recovery as a complex interaction of decreased pain, improved function, and reduced symptom interference with daily life [10]. Common treatments provide mostly small short-term improvements in pain and function, when compared with minimal care [11,12]. Demand for improved treatment effects is pressing. There is a limited understanding of why common treatments are ineffective and a lack of high-quality evidence on promising new treatment targets [13]. Better evidence regarding the mechanisms of treatments can help address these problems and has been identified by pain researchers as one of the highest research priorities [14].

A clearer understanding of the biopsychosocial influences on pain has promoted the development of new explanatory models for CLBP [15] and new treatment strategies [16-19]. Accumulating evidence demonstrates structural, functional, and biochemical differences in the central nervous system between people with CLBP and people without pain [20], many of which appear related to the CLBP experience [21-23]. The RESOLVE trial is a randomized controlled trial (RCT) evaluating a new complex treatment strategy (pain education integrated with graded sensorimotor precision training) partly informed by evidence of central nervous system dysfunction against a sham control.

People with CLBP want improvements in pain and function [10], and the effects of the RESOLVE treatment on these key outcomes will be evaluated [24]. Yet these effect estimates will not elucidate the mechanisms through which the effects occurred. We present an a priori protocol for a secondary analysis of the RESOLVE trial to estimate the effects of the RESOLVE treatment on 7 proposed treatment mechanisms, and to estimate whether these mechanisms cause change in pain and function. The aim of this study is to evaluate these effects through a causal mediation analysis to guide treatment optimization and implementation.

## Methods

### Design

The study involves a causal mediation analysis of a 2-group participant and assessor-blinded RCT [24,25]. The RESOLVE trial was prospectively registered (ACTRN12615000610538) and approved by the University of New South Wales Human Research Ethics Committee (HC15357).

### Participants

Participants were recruited from primary care practices and the community in Sydney, Australia. The eligibility criteria are comprehensively described in the trial protocol [25]. Briefly, the RESOLVE trial included people reporting nonspecific LBP [26] (intensity rated at least 3/10), with or without leg pain, that had persisted for at least 12 consecutive weeks. Participants were aged between 18 and 70, fluent in English, able to access the internet, and had a trusted person to assist with the home portion of the intervention. The RESOLVE trial excluded people with LBP due to serious pathology, and people with contraindications to physical activity, transcranial direct current stimulation, cranial electrical simulation, low-intensity laser therapy, or short-wave diathermy. Finally, the RESOLVE trial excluded people who were pregnant or had given birth in the previous 6 months, had undergone spinal surgery in the previous 12 months, were scheduled for major surgery in the next 12 months, or had an uncontrolled mental health condition that would impede participation.

### Randomization

Eligible participants were randomly allocated in a 1:1 ratio to the RESOLVE treatment or the sham-control treatment. The allocation schedule was generated a priori by a scientist independent to the trial using blocked randomization. The allocations were printed and placed in 276 sealed, opaque, sequentially numbered envelopes. Participants and assessors were blind to both group allocation and study hypotheses throughout the trial and follow-up period.

### Interventions

The treatments are comprehensively described in the trial protocol [25] and briefly here. Each treatment group received twelve 30-60-minute one-on-one treatment sessions with a clinician, scheduled approximately weekly over 12-18 weeks. The treatment sessions were supplemented with a home treatment component entailing 30 minutes of training 5 times per week. Concomitant interventions were allowed and recorded on a weekly treatment diary.

### RESOLVE Treatment Group

The RESOLVE treatment comprised 4 treatment components delivered with a standard progression protocol. The components were pain education, graded sensory training, movement simulation training, and graded precision-focused feedback-enriched functional movement training. The intent was to help people in pain *understand* that it is safe and helpful to move, *feel* safe to move, and *experience* safety with movement as they progress toward reengagement with meaningful functional goals.

Pain education was delivered throughout the treatment period to improve the participants’ understanding of pain and their CLBP problem, address maladaptive beliefs, improve engagement with treatment, and emphasize the value of movement and physical activity. The pain education was based on the *Explain Pain* model [27,28], delivered according to a standard curriculum, and individualized to the patients lived experience and CLBP narrative. The educational material was delivered by the study clinicians and included the use of graphical media, video, metaphor, and narrative [27,29,30].

Sensory precision training comprised tactile localization training, discrimination of sharp/blunt sensations, and graphesthesia training. The movement simulation component was grounded in graded motor imagery, developed for pathological limb pain [31], and included left–right recognition training using the Recognise software [32] and implicit and explicit motor imagery training using a series of custom-designed videos on low back movements.

Graded precision-focused feedback-enriched functional movement training included individualized movement training related to the patients’ goals. Training progressed from part practice to whole task practice within a visual and proprioceptive feedback-enriched environment [33].

### Sham Treatment Group

The sham treatment was composed of 3 treatment components to match for time and clinician interaction, individualization, and relevance [34]. These include passive discussion of the participant’s back pain experience, detuned low-intensity laser therapy, and detuned short-wave diathermy. Participants also received a home training program of sham cranial electrical stimulation to control for the home training requirements of the RESOLVE treatment group.

### Mediators, Outcomes, and Confounder

#### Overview

Patient characteristics, outcome measures, mediators, and potential confounders were assessed at baseline. Mediators were assessed again following the twelfth treatment session, approximately 12-18 weeks following allocation. Outcome measures were assessed again 18 weeks following allocation. Participants and outcome assessors were blind to group allocation and study hypotheses.

#### Outcomes

We will consider 2 primary outcome measures for this mediation study:

Average pain intensity over the past week, assessed using an 11-point Numeric Rating Scale (NRS; 0=no pain, 10=pain as bad as it could be) [35], considered a valid, reliable, and responsive measure of pain intensity [36].Function, assessed using the 24-item Roland–Morris Disability Questionnaire [37], considered a valid and reliable measure of low back–related disability [38,39].

#### Mediators

We will investigate 7 hypothesized mediators. A simplified model of the hypothesized causal relationships between the effects of the RESOLVE treatment on the outcomes through the mediator(s) is presented in Figure 1.

**Figure 1 figure1:**
[figure not shown]
Simplified causal pathways for the effect of the RESOLVE treatment on the outcomes, pain intensity and function, via the hypothesized mediators. The mediators are measured at the end of treatment. Outcomes are measured at 18 weeks after randomization. The potential confounders are measured at baseline. The diagram assumes independence of mediators. The treatment–mediator relationship is represented by the blue line from the RESOLVE treatment to the mediators. The mediator–outcome relationship is represented by the blue line from the mediators to the outcomes. The potential confounders of the mediator–outcome relationship are represented by the red lines. The direct effect of treatment on the outcome is represented by the yellow line.

The 7 mediators to be modeled are as follows:

Tactile acuity: measured using a digital caliper to establish 2-point discrimination thresholds over the lumbar region of most discomfort [40], considered a reliable measure of tactile acuity [41].Lumbopelvic motor coordination: measured on a clinical scale assessing the ability to dissociate lumbopelvic movement from that of the thoracolumbar junction, considered a reliable measure of lumbopelvic control when assessed by an experienced clinician/assessor [42].Back-specific body perception: assessed using the Fremantle Back Awareness Questionnaire (FreBAQ) [43]. The FreBAQ has 9 items, each scored on a 5-point scale (0=Never, 4=Always). The total score ranges from 0 to 36, with higher scores indicating higher body perceptual disturbance. The FreBAQ is considered a psychometrically sound method for assessing disruption of body image in people with CLBP [43].Back beliefs: assessed on the Back Beliefs Questionnaire (BBQ) [44]. The BBQ has 14 items, including 5 distractors, each scored on a 5-point Likert scale (1=completely agree, 5=completely disagree). The total score ranges from 9 to 45, with lower scores indicating more pessimistic beliefs about the consequences of LBP. The BBQ is a valid and reliable measure to quantify beliefs about the consequences of LBP [45].Fear of movement-related pain (kinesiophobia): assessed on the Tampa Scale for Kinesiophobia (TSK) [46]. The TSK has 17 items, each scored on a 4-item scale (1=strongly disagree, 4=strongly agree). The total score ranges from 17 to 68, with higher scores indicating greater levels of fear of movement-related pain. The TSK is a reliable and valid measurement tool that provides information on activity avoidance and pathological somatic focus [47].Pain-related self-efficacy: assessed on the Pain Self-Efficacy Questionnaire (PSEQ) [48]. The PSEQ has 10 items, scored on a 7-point Likert scale (0=not confident at all, 6=completely confident). The total score ranges from 0 to 60, with higher scores indicating greater confidence in the ability to undertake activities despite pain. The PSEQ has adequate psychometric properties [49,50].Pain catastrophizing: assessed on the Pain Catastrophizing Scale (PCS) [51]. The PCS has 13 items, scored on a 5-point scale (0=not at all, 4=all the time). The total score ranges from 0 to 52, with higher scores indicating an exaggerated perception of pain-related problems. The PCS is a reliable measure to assess catastrophic thoughts about pain [51,52].

#### Confounders

We assumed no confounding of the treatment–mediator and treatment–outcome relationships due to random allocation of treatment. We identified potential confounders of the mediator–outcome relationship using the disjunctive cause criterion [53,54]. This involved selecting measured pretreatment covariates that are hypothesized to be a cause of the mediator, outcome, or both. The minimum sufficient adjustment set includes age, biological sex, duration of LBP episode, number of previous LBP episodes, number of other painful areas, work status, injury compensation, education level, depression, concern of LBP severity, sleep difficulty, and pain biology knowledge (refer to Multimedia Appendix 1 for details on potential confounders). We will also include pretreatment measures of the mediators and outcomes in the models [55].

### Causal Mediation Analysis: Rationale

We will test the mechanisms of the RESOLVE treatment strategy for adults with CLBP by estimating the extent to which the 7 hypothesized mediators explain the effect of the treatment on the participants’ pain and disability scores. Using causal mediation analysis, we will partition the total effect (TE) of the treatment into an indirect effect which operates through the mechanism(s) of interest, and a direct effect which operates through all other possible mechanisms [56,57].

The RESOLVE treatment strategy was designed around the Maladaptive Perceptions Model [58], an explanatory framework for the development and persistence of LBP that is grounded in a broad scope of literature concerning behavioral (eg, movement avoidance), neurobiological (eg, altered cortical representations), and cognitive (unhelpful and inaccurate beliefs about the biology of pain and the structural integrity of the back) characteristics of CLBP [20]. The RESOLVE treatment integrates contemporary understandings of pain with known features of best practice care to address the biopsychosocial contributors to the CLBP experience, including maladaptive conceptualizations of the pain problem [59-61], altered sensory function [62,63], altered motor function [64-68], and altered self-perception of the back [43].

While the causal mechanisms that underpin improvement or recovery from CLBP are not well established [13], the Maladaptive Perceptions Model [58] proposes several intermediary variables through which effects might occur. These are cognitions about the back, pain, and movement [69]; back-specific body representations [43]; fidelity and weighting of sensory information from the back [70,71]; and spinal control, movement coordination, and functional tolerance for meaningful activities [33,72]. Components of the RESOLVE treatment were designed to target these factors alongside pain and function.

We have chosen the proposed mediators, pain self-efficacy, back beliefs, pain catastrophizing, kinesiophobia, back perception, tactile acuity, and movement coordination, based on theoretical predictions from the Maladaptive Perceptions Model [58] and the results of pilot studies [33,69-71,73,74].

### Effects of Interest

We will estimate the effect and corresponding uncertainty for the treatment–mediator relationship. This is the average unstandardized effect of the RESOLVE treatment on each independent mediator, compared with sham control. We will also estimate the effect and corresponding uncertainty for the mediator–outcome relationship. This is the average unstandardized effect of the mediator on the outcome (Figure 1).

If inference is considered feasible given the causal assumptions, we will also estimate natural (in)direct effects of the RESOLVE treatment on the outcomes considering (1) the mediators independently, while assuming independence of the mediators, and (2) the mediators simultaneously as a joint mediator.

### Causal Model

The identification of natural (in)direct effects relies on several strong and untestable causal assumptions including (1) no treatment–outcome confounding, (2) no mediator–outcome confounding, (3) no treatment–mediator confounding, and (4) no mediator–outcome confounder that is itself affected by the treatment [75]. Adjustment for a sufficient set of observed confounders and correct specification of the statistical models may provide sufficient conditions to identify mediation effects and causal interpretation [76]. Assumption (4) may not hold because there are possible causal relationships between mediators. We will also assess the mediators simultaneously as a joint mediator which relies on weaker assumptions for identification [77,78]. The causal model is presented in Figure 1.

### Statistical Analysis

Analyses will be performed in R (version 3.6.1; R Foundation for Statistical Computing) [79]. We will use the “mediation” package [80] to estimate independent mediated effects and the “medflex” package [78] to estimate joint mediated effects.

We will estimate effects for the treatment–mediator and mediator–outcome relationship with 2 regression models: the mediator model and the outcome model. We will specify the mediator model as a linear regression of the mediator (dependent variable) on treatment allocation and baseline values of the mediator. The outcome model will be specified as a linear regression of the outcome at 18 weeks (dependent variable) on the mediator at baseline and follow up, treatment allocation, and possible confounders of the mediator-outcome relationship, and a treatment allocation x mediator interaction term. We will also include an interaction term (treatment allocation × mediator) in the outcome models to increase model flexibility [57].

### Independent Mediated Effects

A model-based inference approach developed by Imai et al [81] will be used to estimate independent mediated effects for each mediator. We will use the “mediate” function [80] to compute the average treatment effect, the average causal mediation effect (ACME), and the average direct effect (ADE). We will use 1000 bootstrapped simulations to estimate 95% CIs. We will interpret conditional estimates of the ACME and ADE separately if there is evidence for a significant (*P*<.05) intervention–mediator interaction. If there is no evidence for an interaction, we will interpret the average of the conditional effects for the ACME and ADE.

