## Results

A total of 276 participants have been randomized into the RESOLVE trial. Follow-up data collection is underway with authors blind to study data.

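### An interaction test at P<.05 decides, across 14 models, whether averaged or arm-specific ACME/ADE carry the interpretation, and arm-specific effects selected this way are exaggerated

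*Protocol article*

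**What the plan says.** The rule is in the protocol article, Independent Mediated Effects: "We will interpret conditional estimates of the ACME and ADE separately if there is evidence for a significant (*P*<.05) intervention–mediator interaction". If the test is not significant, "If there is no evidence for an interaction, we will interpret the average of the conditional effects for the ACME and ADE".

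Under Statistical Analysis the interaction is part of the outcome model whatever the test shows: "We will also include an interaction term (treatment allocation × mediator) in the outcome models to increase model flexibility".

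The number of decisions follows from three places: "We will investigate 7 hypothesized mediators" (Mediators), "We will consider 2 primary outcome measures for this mediation study" (Outcomes), and the statement that the model-based approach "will be used to estimate independent mediated effects for each mediator" (Independent Mediated Effects). The article names no main ACME/ADE estimate that applies whatever the test result. It states no power or error rate for the interaction tests.

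**The concern.** A preliminary test is often used to decide whether a term can be dropped. Here nothing is dropped. The same model is fitted either way, and the P value only decides whether the reader is directed to one averaged effect or to two arm-specific effects.

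Three things follow:

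- Some models will switch by chance when there is no interaction.
- A real but modest interaction will often be missed, and the rule then proceeds as if there were none.
- When the rule does direct the reader to the arm-specific effects, it does so because their estimates happen to lie far apart. Effects chosen for that reason are exaggerated, and their ordinary 95% CIs make no allowance for the choice.

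The practical risk is that a chance split between arms is taken for a mechanism that works in one arm and not the other, in a study meant to guide refinement of the treatment.

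**Working it through.** The article gives no figure for this rule, so there is none to reproduce.

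**Inputs from the article.** 7 mediators; 2 primary outcomes; threshold .05 (taken as two-sided); 276 randomised 1:1, so 138 per arm. Complete-case analysis is allowed below 15% missing, so the smaller case is 138 × 0.85 ≈ 117 per arm.

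**Assumptions (not in the article).** Mediator and residual SD of 1. In the simulations: treatment–mediator effect a = 0.5, mediator–outcome slope b = 0.3, no covariates, and delta-method rather than bootstrap CIs.

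**1. Number of decisions.** 7 × 2 = 14.

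**2. Chance switches with no true interaction.**
- Expected number: 14 × 0.05 = 0.70, whatever the correlation between models.
- At least one, if independent: 1 − 0.95^14 = 0.51. At least two: 0.15.
- At least one, by simulation with correlated mediators and outcomes (n = 276, 2,000 runs): 0.44 (correlations 0.3 and 0.5), 0.39 (0.5 and 0.5), 0.29 (0.7 and 0.6).

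**3. Probability that a true interaction is detected.** For a slope difference d between arms, SE = √(2/n per arm). At 138 per arm SE = √(2/138) = 0.120. Power = Φ(d/SE − 1.96) + Φ(−d/SE − 1.96).

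| d | 138 per arm | 117 per arm |
|---|---|---|
| 0.1 | 0.13 | 0.12 |
| 0.2 | 0.38 | 0.33 |
| 0.3 | 0.70 | 0.63 |

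Simulation of the fitted model at 138 per arm gave 0.13, 0.37–0.38 and about 0.69.

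**4. Exaggeration after selection.** ACME(1) − ACME(0) = a × d. To reach P<.05 the estimated slope difference must exceed about 1.96 × 0.120 = 0.236, so the estimated ACME contrast must be about 0.5 × 0.236 = 0.118 or more in size, whatever the truth.
- True contrast 0: mean absolute contrast among significant runs 0.142.
- True contrast 0.5 × 0.1 = 0.05: mean contrast among significant runs about 0.145, nearly three times the truth.
- True contrast 0.5 × 0.3 = 0.15: mean among significant runs 0.18, so the exaggeration shrinks as the interaction grows.

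The ADE contrast is affected in the same way. The total effect equals both ACME(1) + ADE(0) and ACME(0) + ADE(1), so ADE(1) − ADE(0) = ACME(1) − ACME(0).

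**5. Coverage of nominal 95% CIs for the ACME, no true interaction.**

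| Estimate | All runs | Runs with P<.05 |
|---|---|---|
| Arm-specific ACME | about 93% | about 76–80% |
| Average ACME | about 94% | about 93–94% |

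**6. Bias of the average ACME.** True value 0.150; mean 0.150 when the test is non-significant and 0.151 when significant. The test does not distort it.

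**The case against.** The best defence is that the rule is prespecified, follow-up was still under way with the authors blind to the data, and the fitted model never changes, so the usual harm of pre-testing, a biased estimate from a wrongly simplified model, does not arise. That stands, and step 6 confirms it for the average ACME.

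Three stronger readings are tempting, and the article does not support them.

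- *That different pairs will be reported on different effects.* The article says which effects will be interpreted, not that the others will be withheld. All of them may still be tabulated.
- *That comparison between mediators becomes invalid.* With no interaction the arm-specific and averaged effects have the same true value, so a chance switch costs precision and may suggest a spurious arm difference, but it does not aim at a wrong quantity. The article also sets no aim of formally ranking mediators.
- *That the 95% CIs in general fail to cover as stated.* The loss is confined to arm-specific effects in models where the test was significant. Over the whole procedure with no interaction, simulated coverage was 0.925–0.928 against 0.936 for the average ACME alone, a loss of about one point.

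The 0.51 is also an upper figure, since it needs 14 independent tests, and the article itself allows for causal relationships between mediators. Finally, where a real interaction exists an average can hide differing arm-specific effects, so an average headline is a convention with its own limit.

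What remains is that the rule moves the reader away from a stable estimate and towards distorted ones in just those models where noise, or noise added to a small interaction, has pushed the arms apart. Prespecification does not remove that.

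**Conclusion.** The point holds in this limited form and is worth correcting, at moderate severity. The rule, the retained interaction term and the count of 14 come straight from the article. The expected 0.7 chance switches depend only on the .05 threshold and the absence of interaction.

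The other figures rest on assumptions. The 0.29–0.44 depends on assumed correlations. The detection probabilities depend on SDs of 1 and fall somewhat with missing data. The exaggeration and the 76–80% coverage depend on the assumed effects of 0.5 and 0.3 and on delta-method CIs in place of the planned bootstrap. Coverage was checked for the ACME only. The direction does not turn on the exact values: for small to moderate interactions, which effect is interpreted is largely a matter of chance, and those picked out by P<.05 are overstated.

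**What to change.** Delete the P<.05 switch in Independent Mediated Effects and replace it with wording such as: *For all 14 mediator–outcome pairs the average ACME and ADE are the main estimates. The ACME and ADE under each arm, and the interaction coefficient, will be presented with 95% CIs for every pair regardless of significance.*

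The model, the data and the bootstrap stay as planned. The cost is two sentences and a larger table. The average must be read beside the arm-specific effects where a real interaction exists, which the always-presented columns allow. With one main estimate fixed in advance, the expected number of chance switches falls from 0.70 to 0.
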